### Data Collection

Data collection will take place for one week in each month of the year for 18 months starting March 2021, resulting in 18 designated weeks of data collection. This will permit evaluation of the variation in morbidity through the fifth and most serious wave of the COVID-19 pandemic in Hong Kong and across seasons, which has been a significant consideration in previous studies. Seasons may be divided into 3-month periods based on historical climatological data with spring as March-May, summer as June-August, autumn as September-November, and winter as December-February. Thus, there will be 3 weeks of data collection in each season. The study will run over 18 months to capture temporal trends as well as seasonal variation of diseases such as influenza. The first full week of each month in which there are no public holidays will be designated as the data collection week to maximize the number of working days. The week will be defined as 7 consecutive days from Sunday-Saturday as most private doctors in Hong Kong work on weekends and public GOPC are open for a half-day on Saturday. Each participating doctor will collect data on consecutive patients during any of the designated weeks of each season for a total of 6 weeks of data collected per doctor. The research team will collect all completed forms after each data collection week. All data will be checked for proper coding and be doubly entered, cleaned, and compiled into a central database for analysis.

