### Data Analysis

The patterns of morbidity in primary care will be presented by descriptive statistics for the prevalence of health problems and diseases, as well as the rates of management activities (referral, investigation, prescription, preventive care), weighted for the proportion of private and public primary care doctors in Hong Kong. The pattern of morbidity will be compared with the previous pattern in 2007-2008. All estimates will be accompanied by 95% CIs.

Stratified estimates in the patterns of morbidity in primary care by public and private doctors will also be reported and compared with the previous pattern in 2007-2008. The influence of the health care sector on morbidity patterns will be assessed by comparing the prevalence and rates of public and private doctors by nonlinear mixed effects analysis with logit link that accounts for potential covariance among health problems from the same doctor.

Factors associated with morbidity and management patterns in primary care will be assessed by nonlinear mixed effects model with logit link to cater for the dichotomous outcomes. Potential factors including patient demographics (age, sex), doctor background characteristics (age, qualifications, years of practice, type of practice, average number of consultations, participation in primary care initiatives), and nature of problem (acute, chronic, preventive) will be taken as covariates in the model. Both univariable and multivariable analyses will be performed. In the multivariable analysis, the presence of multicollinearity will be assessed by examining the tolerance. Factors involved in multicollinearity will only be considered one at a time.

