## Results

Data collection started March 1, 2021. As of April 2022, 176 doctor-weeks of data have been collected. The data collection will continue until August 31, 2022.

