On the other hand, practice-based morbidity surveys are a feasible option for capturing accurate and more comprehensive data [25]. They allow documentation of actual consultations, reflecting the patient’s reason for seeking care and the doctor’s diagnostic interpretation of the illness, which can be standardized by validated tools [16]. Both of these features are essential in health care service planning, which must rely on accurate information about health problems but also consider patient need. Because of this, such surveys continue to be used on a large scale in the United States, where the Centers for Disease Control and Prevention initiated the National Ambulatory Medical Care Survey in 1973 and has been running it annually since 1989 [26]. In Australia, the Bettering the Evaluation and Care of Health program collected general practitioner–patient encounter data for 18 years until 2016. These data were used widely for policy development and to improve Australian health care delivery and patient care [27]. Practice-based morbidity studies conducted in primary care settings have proven (and continue) to be a useful and reliable methodology for documenting disease prevalence and for service planning [6,10,28-32].

An issue that we encountered in the sample size calculation was whether we could assume that the number of health problems needed to encounter in each season should be evenly distributed. Such an assumption may not necessarily be reasonable, particularly for some season-specific diseases. However, based on the raw data of the earlier Hong Kong morbidity study, the overall most commonly occurring diagnosis was upper respiratory infection (26.4% of encounters), which was also the most commonly occurring diagnosis in all 4 seasons, ranging in frequency from 32.1% in winter to 22.7% in spring. The 14 diagnoses that account for >1% of visits were the same top 14 diagnoses across all 4 seasons and there was only variation in the order of frequency in each season. This is consistent with data from a study on the seasonal variation in diagnoses in primary care based on the United States National Ambulatory Medical Care Survey [33]. The key finding was that there was little seasonal variation among the 23 most commonly occurring diagnoses (which accounted for >1% of encounters)—only the rank order of the diagnoses varied from season to season.

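### The 18-month window covers spring and summer twice, but the stated weights are by sector only, so pooled estimates of seasonal diagnoses and their change since 2007-2008 can be shifted

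*Protocol article*

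**What the plan says.** - **Window.** Data Collection: "Data collection will take place for one week in each month of the year for 18 months starting March 2021". Results confirms the end date: "The data collection will continue until August 31, 2022".
- **Seasons.** Data Collection defines "spring as March-May, summer as June-August, autumn as September-November, and winter as December-February", and continues: "Thus, there will be 3 weeks of data collection in each season".
- **Per doctor.** Each doctor records "during any of the designated weeks of each season for a total of 6 weeks of data collected per doctor".
- **Weighting.** Data Analysis gives one weight for the prevalence and rate estimates: "weighted for the proportion of private and public primary care doctors in Hong Kong". It names no season weight, lists no season term among the model covariates, and does not restrict any estimate to 12 months.
- **Comparison.** Data Analysis: "The pattern of morbidity will be compared with the previous pattern in 2007-2008". Sample Size Calculation describes the 2007-2008 data as collected over one year.
- **Seasonality.** In the Discussion (Overview), URI made up 26.4% of encounters overall in the earlier survey, "ranging in frequency from 32.1% in winter to 22.7% in spring".

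**The concern.** Eighteen months from March contain two springs, two summers, one autumn and one winter. Spring and summer thus supply 12 of the 18 designated weeks (two thirds, against one half in a full year), and winter supplies 3 of 18 (one sixth, against one quarter). The schedule of each doctor repeats this mix: two spring weeks, two summer weeks, one autumn and one winter.

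A pooled figure weighted only by sector is therefore not an annual figure. For a diagnosis that peaks in winter it is too low. Set against a one-year survey, the shortfall reads as a decline since 2007-2008, and change since that survey is the study's stated aim. More data of the same mix would not reduce the shift. The article does state a weighting rule, and that rule does not suit the window it is applied to, so this is more than a detail left to a fuller document.

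**Working it through.** **The plan's own figures.** Sample Size Calculation uses p = 50%, 95% confidence and a maximum error of 0.5 points. n = 1.96² × 0.5 × 0.5 / 0.005² = 38,415, as stated. With 40 doctor-weeks × 250 problems = 10,000 per season and one-third dropout, 40 / (2/3) = 60 doctor-weeks, also as stated.

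**Season counts.** Applying the season definitions to March 2021 to August 2022 gives spring 6, summer 6, autumn 3 and winter 3 weeks, total 18.

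**Shift from pooling.** With equal data per designated week:
- Pooled = (2 × spring + 2 × summer + autumn + winter) / 6
- Equal-season mean = (spring + summer + autumn + winter) / 4
- Shift = pooled - mean = (spring + summer - autumn - winter) / 12

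**Direction for URI.** Spring is the lowest season and winter the highest. So spring cannot exceed autumn, summer cannot exceed winter, and the shift cannot be positive if the 2007-2008 seasonal rates still hold. It is zero only if autumn equals spring and summer equals winter.

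**Size for URI.** Inputs from the Discussion are overall 26.4%, spring 22.7% and winter 32.1%. Summer and autumn are not given. Assume that 26.4% is the equal-season mean and that both missing values lie between 22.7% and 32.1%. Then summer + autumn = 4 × 26.4 - 22.7 - 32.1 = 50.8, and pooled = (2 × 22.7 + summer + 50.8 + 32.1) / 6 = (128.3 + summer) / 6.

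| Summer | Autumn | Pooled | Shift (points) |
|---|---|---|---|
| 22.7 | 28.1 | 25.17 | -1.23 |
| 25.4 | 25.4 | 25.62 | -0.78 |
| 27.1 | 23.7 | 25.90 | -0.50 |
| 28.1 | 22.7 | 26.07 | -0.33 |

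The shift is larger than 0.5 points when summer is below 27.1%, which is most of the admissible range of 22.7% to 28.1%.

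**Without the equal-season assumption.** Summer minus autumn may lie anywhere from -9.4 to +9.4, so the shift (22.7 - 32.1 + difference) / 12 runs from -1.57 to 0.

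**Sampling error for scale.** At p = 26.4%, under simple random sampling, the 95% half-width is 0.44 points with 38,415 problems. With 60,000 (six season-periods of 10,000) it is 0.35.

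**Cost of equal-season weighting.** The four spring and summer periods get weight 0.5 each, and autumn and winter get 1 each. Kish effective number = (4 × 0.5 + 2)² / (4 × 0.25 + 2) = 16 / 3 = 5.33 of 6 periods, or 89%. On 60,000 problems that is about 53,300.

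**The case against.** The strongest reply is that the article never says outright that all 18 months go into one estimate. It sizes the study over one year, gives temporal trends and seasonal variation as the reason for the longer window, and lists seasonal variation as a secondary outcome. That stands as a caution. But Data Analysis offers no other rule for the primary estimates, and a separate seasonal outcome does not correct them.

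Four stronger readings are tempting and are not supported:

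- **That the shift definitely exceeds the stated error.** The range straddles 0.5 points because the summer and autumn shares are not given.
- **That pooled prevalence in general is biased.** Seasonal percentages are given for URI only. Outcomes with little seasonality would hardly move, and no figure shows a spurious rise in a spring or summer disease. The Discussion argues that mainly the rank order of the leading diagnoses varies by season. Stable rank does not mean stable prevalence, however: URI itself differs by 32.1 - 22.7 = 9.4 points between winter and spring.
- **That three weeks per season contradicts 18 weeks.** Counting the two springs and two summers separately, 6 periods × 3 weeks = 18, and one week per period gives 6 weeks per doctor. The text is consistent on that reading.
- **That calendar months must also be balanced.** Doctors may choose any designated week in a season. With 12 public doctors, or 8 after one-third dropout, a season's month would have about 2.7 to 4 public doctors, so month-by-sector weights would be unstable or undefined.

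Three further points stand in part:

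- **Baseline season mix.** It is unknown. At 250 problems per week, 69,973 / 109 / 250 = 2.6 weeks per doctor, so the average doctor did not cover four seasons.
- **The 0.5-point benchmark.** It ignores clustering within doctor. As an illustration with an assumed intraclass correlation of 0.005, 40 doctors × 1,500 problems give a half-width of about 1.0 point, since 0.35 × √(1 + 1,499 × 0.005) = 1.0. A wider interval may hide the shift but does not remove it.
- **The pandemic.** The Limitations section discloses altered care-seeking, and season weighting will not remove that effect. The season mix is a separate problem that the analysis can remove.

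**Conclusion.** The concern holds for seasonal diagnoses, conditional on the 18 months being pooled as the text implies. The 6/6/3/3 imbalance, the sector-only weight and the one-year comparator are all in the document. For URI, pooling would turn 26.4% into about 25.6% with no true change: -0.8 points, range -0.3 to -1.2. This rests on equal seasons in 2007-2008, unchanged seasonal rates and equal data per designated week. Dropping the equal-season assumption widens the range to between 0 and -1.6. The shift can exceed the planned 0.5-point error but is not shown to do so in every case. For management rates and other diagnoses the document gives no seasonal figures, so no size can be stated.

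**What to change.** Add to Data Analysis that annual prevalence and management rates, and the comparison with 2007-2008, give the four seasons equal weight within each sector before the sector weight is applied. If the 2007-2008 season mix is known and unequal, match it for the comparison.

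Alternatively, base the annual estimate and the comparison on 12 consecutive months, chosen without reference to the results. Under either option, report the repeated spring and summer separately, which also serves the seasonal outcome. State in Data Collection that the three weeks refer to each of six season-periods. Do not add calendar-month balancing.

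Cost: season weighting loses about 11% of effective sample size, leaving about 53,300 of 60,000 planned problems against the required 38,415. The 12-month option leaves one third of the data out of the annual estimate, so 4 × 10,000 = 40,000 remain, only just above the requirement. Neither needs new data.

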### Data Collection Forms and Tools

#### Background Information Form

Each doctor participating in the study will provide background information including demographics, practice characteristics, training, and involvement in government-coordinated primary care initiatives. To maintain anonymity, doctors will be allocated a unique identifier to link their background information with the patient encounter data collected.

#### Encounter Form

Doctors will manually record information on every patient encounter that occurs during the designated data collection week on a standard data collection form. The information on this form includes basic patient demographics (age and sex), whether he/she is a new patient, the presenting problem as stated by the patient, the diagnosis (or corresponding International Classification of Primary Care, Second Edition [ICPC-2] code) as determined by the doctor, the management activities undertaken, drugs prescribed, and preventive care interventions initiated. Doctors can complete most of the form with checkmarks or simple abbreviations and can write in the diagnosis/problem if they are not sure of the ICPC coding. Doctors in the public sector GOPC are already using ICPC coding in their usual practice and may find it routine to record diagnoses in this way. For forms completed with written diagnoses, trained research assistants will translate these to the corresponding ICPC codes.

#### ICPC-2

ICPC-2 is the most widely used international classification for systematically capturing and ordering clinical information in primary care [15]. The ICPC-2 is widely used in general practice for the classification of three important elements of the health care encounter: reasons for encounters, diagnoses or problems, and processes of care.

### Outcome Measures

#### Primary Outcomes

Prevalence of health problems and diseases presenting in primary careRates of management activities including referral, investigation, prescription, and preventive care intervention by primary care doctorsDistribution of health problems and diseases presenting in the public compared with the private primary care settingFactors that affect the proportion and distribution of health problems in the public sector compared with the private sector

#### Secondary Outcomes

Prescription rates of specific classes of drugsSeasonal variation in primary care morbidity patternRelationship between patient’s presenting problem and doctor’s diagnosis

#### Confounding Variables

Demographic information of patientsPractice sectorNature of the health problem (acute or chronic)Background characteristics of the doctor and the practice

### Data Analysis

The patterns of morbidity in primary care will be presented by descriptive statistics for the prevalence of health problems and diseases, as well as the rates of management activities (referral, investigation, prescription, preventive care), weighted for the proportion of private and public primary care doctors in Hong Kong. The pattern of morbidity will be compared with the previous pattern in 2007-2008. All estimates will be accompanied by 95% CIs.

Stratified estimates in the patterns of morbidity in primary care by public and private doctors will also be reported and compared with the previous pattern in 2007-2008. The influence of the health care sector on morbidity patterns will be assessed by comparing the prevalence and rates of public and private doctors by nonlinear mixed effects analysis with logit link that accounts for potential covariance among health problems from the same doctor.

Factors associated with morbidity and management patterns in primary care will be assessed by nonlinear mixed effects model with logit link to cater for the dichotomous outcomes. Potential factors including patient demographics (age, sex), doctor background characteristics (age, qualifications, years of practice, type of practice, average number of consultations, participation in primary care initiatives), and nature of problem (acute, chronic, preventive) will be taken as covariates in the model. Both univariable and multivariable analyses will be performed. In the multivariable analysis, the presence of multicollinearity will be assessed by examining the tolerance. Factors involved in multicollinearity will only be considered one at a time.

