Since the last morbidity study in Hong Kong in 2007-2008 [3], the Hong Kong Government has implemented some primary care initiatives in response to the increasing burden on public general outpatient clinics (GOPC) such as the GOPC Public-Private Partnership, Elderly Health Care Voucher Scheme, and the Vaccination Subsidy Scheme. These aim to encourage patients to seek care in the private sector, particularly for care of chronic diseases. Tracking morbidity and management trends would provide an indication of the impact of these initiatives on the prevalence of chronic disease and its care in both public and private primary care sectors.

Apart from the morbidity pattern, specific information on the management pattern such as prescription, investigation, referral to specialists, health promotion, and disease prevention is important for assuring the quality of primary care services and for identifying support services needed. In 2014-2015, there were an estimated 6 million primary care encounters in the public sector alone [11], which extrapolates to about 30 million primary care encounters in the combined public (20% of total encounters) and private sectors across Hong Kong [12]. The most recent morbidity study found that the Hong Kong referral rate to specialists was 2.5% in 2007-2008 [3], which means that even a small increase of 1% in referral rate would produce a huge relative increase of 40%, translating to an additional 300,000 specialist referrals. Changes in consultation trends in primary care do occur [13], with substantial potential impact on health care service needs and expenditures, and must be monitored.

With an aging population, increasing prevalence of chronic disease, and the implementation of primary care initiatives to shift some of the burden of chronic disease care from the public to the private sector, a primary care morbidity study is timely and important to document and evaluate the impact of these changes.

This study aims to determine the changes in morbidity and management patterns in Hong Kong primary care compared with the patterns identified in the morbidity study conducted in 2007-2008 [3]. Specific objectives include the following:

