### Sample Size Calculation

The sample size calculation is based on the first two primary objectives of our study, which are to determine the proportion of health problems/diagnoses among all clinical encounters and the proportion of various management activities in terms of prescription, investigation, referral, and preventive care. The 2007-2008 morbidity study found that respiratory conditions comprised the largest proportion of problems (36.2%) and among these, upper respiratory tract infection was the most common diagnosis (26.4%) [10]. On this basis, if we conservatively anticipate the proportion of a type of health problem/diagnosis to be 50% with a confidence interval of 95% and a maximum error of 0.5%, we will need to encounter at least 38,415 health problems over one year. This translates to about 10,000 health problems per season. In the 2007-2008 morbidity study, 109 doctors recorded 69,973 health problems over the course of the year, which meant that on average, each doctor encountered about 250 health problems in one week. Based on this estimation, 40 doctor-weeks will be required to encounter the requisite number of health problems for each season. Assuming there is a one-third dropout rate of doctors, 60 doctor-weeks per season will be required. According to a general population study on service utilization patterns in primary care, around 80% of those who visit a Western medical practitioner would attend a private clinic whereas the remaining 20% would attend publicly funded primary care services [12]. Considering this, we need 48 doctors from the private sector and 12 doctors from the public sector to participate in the study.

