## Discussion

### Overview

In determining the approach for this study, we reviewed different data collection methods for morbidity and clinical practice in primary care to support the conceptualization and methodology selected. Commonly used approaches in gathering health and health service data in primary care include population surveys, retrospective analysis on medical records or registers, and practice-based morbidity surveys using patient encounter forms. However, methodological or practical considerations may limit the usefulness of any of these methods.

Population surveys such as general household surveys about individual health conditions and health service usage provide a broad-based perspective, where health problems that have not been consulted can also be identified [16]. However, the reporting relies on patient recollection [17], and the accuracy of morbidity identification largely depends on patient’s knowledge. Underreporting is also expected, especially for “sensitive” diseases such as sexually transmitted infections and cancer [16], or among older adult patients [18].

Data drawn from electronic medical records or registers of patient health care information provide rich databases for evaluating disease prevalence and morbidity trends in primary care as demonstrated in various international studies [19-24]. The data obtained are mostly accurate for medically diagnosed health problems. However, in the absence of centralized computerized databases, data retrieval may be difficult and labor intensive [25]. This is the case in Hong Kong, where centralized systems capture data only for the public government GOPCs, which provide only 20% of primary care.

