As our sample size calculation is based on the primary objective of the study, which is to determine the prevalence of health problems/diagnoses among all clinical encounters, the calculation is derived from the proportion of the most commonly occurring diagnosis encountered in the earlier morbidity study. Since the most commonly occurring diagnosis accounts for 22.7%-32.1% of encounters in any given season, the conservative estimate of 50% that we used in our sample size calculation is reasonable to calculate the total number of health problems needed to encounter per season.

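### Pooled estimates are weighted to the sector share of doctors although the target is a proportion among encounters, so the sector mix may be wrong, depending on how the weight is applied

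*Protocol article*

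**What the plan says.** The Data Analysis section says that the pooled prevalences of health problems and the pooled rates of management activities will be "weighted for the proportion of private and public primary care doctors in Hong Kong". It does not say whether this weight multiplies sector-level estimates or is attached to each doctor. The same section also promises separate public and private estimates and a mixed model comparing the sectors.

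The target is defined on encounters. The Sample Size Calculation gives the first primary objective as to "determine the proportion of health problems/diagnoses among all clinical encounters", and the Discussion (Overview) repeats it: "to determine the prevalence of health problems/diagnoses among all clinical encounters".

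Every sector share in the article is on the utilisation side:

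- Introduction: "about 30 million primary care encounters in the combined public (20% of total encounters) and private sectors".
- Sample Size Calculation: "around 80% of those who visit a Western medical practitioner would attend a private clinic", with the remainder in publicly funded care.
- Discussion (Overview): "public government GOPCs, which provide only 20% of primary care".

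The attendance share is then carried over to recruitment: "we need 48 doctors from the private sector and 12 doctors from the public sector". No public/private share of Hong Kong primary care doctors is given, and the workload of about 250 problems per doctor-week is not split by sector.

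**The concern.** The weight and the target refer to different populations. A share of doctors and a share of encounters agree only if doctors in the two sectors have the same caseload. The article gives no reason to assume this: it lists the average number of consultations as a doctor characteristic for the models, and it describes different weekend working in the two sectors.

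Case mix is expected to differ by sector. The Introduction says that most chronic-disease patients are seen in public clinics, and the public/private contrast is itself a primary outcome. A wrong sector weight would therefore shift pooled prevalences and management rates, which are primary outcomes, and a larger sample would not reduce the shift. The study is sized for a maximum error of 0.5 points, and the Introduction treats a 1-point change in the referral rate as 300,000 additional referrals, so an error of that order would matter.

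**Working it through.** **The plan's own figures.** For p = 0.5, 95% confidence and maximum error 0.005: n = 1.95996² × 0.25 / 0.005² = 38,414.6, rounded up to 38,415, as stated. Per season 38,415 / 4 ≈ 9,604, taken as 10,000. Then 10,000 / 250 = 40 doctor-weeks, and 40 / (1 − 1/3) = 60. The split is 60 × 0.8 = 48 private and 60 × 0.2 = 12 public. The encounter total also reproduces: 6 million / 0.20 = 30 million. The 48/12 step turns a share of attendance directly into numbers of doctors.

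**Inputs for the check.** Public share of encounters 0.20 (Introduction). Public share of doctors D: not in the article, assumed 0.10 to 0.50. Public-minus-private difference in prevalence: not in the article, assumed 5, 10 or 20 points.

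**Reading A: D multiplies sector-level estimates.** The pooled figure is D × p_pub + (1 − D) × p_priv. The target is 0.20 × p_pub + 0.80 × p_priv. Subtracting,

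error = (D − 0.20) × (p_pub − p_priv).

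The last column is the public/private caseload ratio that would reconcile D with a 20% encounter share, (0.20 / 0.80) / (D / (1 − D)).

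| D | 5-point gap | 10-point gap | 20-point gap | caseload ratio implied |
|---|---|---|---|---|
| 0.10 | −0.5 | −1.0 | −2.0 | 2.25 |
| 0.15 | −0.25 | −0.5 | −1.0 | 1.42 |
| 0.20 | 0 | 0 | 0 | 1.00 |
| 0.25 | +0.25 | +0.5 | +1.0 | 0.75 |
| 0.30 | +0.5 | +1.0 | +2.0 | 0.58 |
| 0.40 | +1.0 | +2.0 | +4.0 | 0.38 |
| 0.50 | +1.5 | +3.0 | +6.0 | 0.25 |

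Errors are in percentage points. At D = 0.10 or 0.30, a 5-point gap already uses the whole 0.5-point margin. The largest errors need D near 0.50, where a public doctor would see only a quarter of a private doctor's volume.

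**Reading B: a weight per doctor, all recorded encounters counted.** Give each of 12 public doctors weight D/12 and each of 48 private doctors (1 − D)/48, and let r be the public/private ratio of recorded volume per doctor. The implied public encounter share is

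D × r / (D × r + 1 − D).

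This equals the population encounter share whenever r among the recruited doctors equals r in the population. For example, D = 0.30 and r = 0.5 gives 0.15 / 0.85 = 0.1765, and D = 0.10 and r = 2 gives 0.20 / 1.10 = 0.1818; both match the true share although D differs from it.

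If the recruited ratio differs, the recovery fails. Suppose D = 0.30 and the true ratio is 0.583, so that the true share is 0.20. If recruited doctors record equal volumes (r = 1), the implied share is 0.30, and a 10-point gap is again misstated by (0.30 − 0.20) × 10 = 1.0 point. Only the ratio matters: a departure common to both sectors cancels.

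**The case against.** The strongest reply is that Reading B is the natural one. Doctors are the target population and the recruited unit, and each records consecutive patients. Weighting recruited doctors to the doctor population is then an ordinary cluster weight, and each doctor's own volume carries the encounter mix. A reader might infer from the wording that the pooled figures must have the wrong mix unless doctor and encounter shares coincide. The article does not support that, because under Reading B the shares can differ without error. This part of the reply stands.

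It stands conditionally, however. Recruitment runs through a research network, college members, honorary teachers and voluntary lists; one third of doctors are expected to drop out; and doctors may record in any of the designated weeks of a season. Nothing secures volumes that are typical of each sector.

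A second reply is that a condensed article may leave the mechanics of weighting to a fuller document. That is fair for the mechanics, but the article does fix the basis of the weight, and that basis does not match its stated target.

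A third reply is that the size is conjectural. This is correct: D, sector caseloads and sector prevalences are all absent. A reader might infer that problems commoner in public clinics will be understated; that needs D below 0.20, and above 0.20 the sign reverses. The one doctor split in the article, 48/12, would give no error, although it is a recruitment target and not a population share.

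Finally, the sector-specific estimates, their comparison with 2007-08 and the sector models do not depend on this weight. Nor can one conclude that the pooled comparison with 2007-08 is biased, since that also depends on how the earlier survey was weighted, which is not shown.

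**Conclusion.** The mismatch is real and should be fixed before analysis; confidence is moderate. The pooled estimates are tied to a share of doctors that the article does not give, while their target is among encounters, for which it does give a share.

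If D is applied to sector-level estimates, the error for a 10-point sector gap runs from −1.0 to +3.0 points over the assumed range of D, passing through zero at D = 0.20, against the planned 0.5 points. If the weight is applied per doctor, the encounter mix is right only when the recruited doctors' relative volumes are typical of their sectors. The article neither chooses between these readings nor secures the condition that the second needs. The error is nil for problems equally common in both sectors, and results reported by sector are untouched.

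**What to change.** Define the weight for pooled estimates on the sector share of encounters: the cited 20% public and 80% private or, better, the most recent utilisation figure that covers the same public clinics and the study period. Report how the pooled estimates change over a plausible range of the public encounter share. If per-doctor weights are kept, say so, and compare the encounter mix that they imply with the external share.

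The change costs one sentence and a small sensitivity table; no further data collection is needed. Its drawback is that the external share is imperfect. It rests on 2014-15 public encounters, and the Discussion ties it to general outpatient clinics although the study's public sector also includes Department of Health clinics. Schemes to move patients to private care and the pandemic may also have shifted it. It should therefore not be held fixed within every season without checking, which is the reason for the sensitivity range.
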